#### Description of the programs

Both programs consist of 6 weekly sessions, each lasting ~1 h (shorter in the hypnosis arm), of CRF management over a period of 6 weeks. They focus on CRF and its psychosocial determinants (see **Table 2**):

- Session 1: Patient Education about CRF- Session 2: Work on perceived control- Session 3: Work on emotional regulation- Session 4: Work on social support during illness- Session 5: Working on coping strategies- Session 6: Review of previous exercises/sessions, synthesis

#### CBT

In order to standardize the program, the content of the CBT intervention was inspired by previous studies (Gielissen et al., 2006, 2007; Poort et al., 2017) and based on previous results focusing the psychosocial determinants of fatigue in metastatic CRCm patients (Baussard et al., 2022). In Gielissen et al. (2006) study, the rationale of the intervention was based on the model of precipitating and perpetuating factors, where each session focused on fatigue perpetuating factors such as coping with the experience of cancer, fear of disease recurrence, dysfunctional cognitions concerning fatigue or negative social interactions. Inspired by these studies, each session of the CBT program will focus on fatigue determinants (Table 2).

#### Hypnosis

Hypnosis, as a speech-based therapy, is difficult to standardize. One way to standardize the protocol is to distribute audio-scripts to patients to listen to at home independently (Bragard et al., 2017; Gregoire et al., 2017). However, this way has two main limitations. First, each patient has her/his own vocabulary, that makes uncertain the standardized and general speech-based efficacy. Then, the benefit from the session as if a therapist were present, compared with the benefit from a session with a therapist, may differs (as there is no way to ensure the state of hypnosis or the duration of the session, for example). The (Jensen and Patterson, 2006; Jensen et al., 2008, 2012) ‘s hypnosis included sessions based on a written script that each clinician read to the patients, although minor wording changes were allowed to facilitate verbal flow. In 2013, Montgomery et al. (2013) gave advices for setting up a standardized hypnosis program to facilitate its evaluation: introducing of the session; inducting; working on metaphors or making specific suggestions and then instructing for self-hypnosis or anchoring. Moreover, Grégoire et al. (2022) published a study protocol where hypnosis was proposed in a face-to-face and in a standardized way. Taken as a whole, these works encourage the creation of a specific program with exercises specifically designed to work on a problem-related fatigue as it is the case in the CBT intervention. Description of hypnosis sessions and associated fatigue variables are presented in Table 1.

1. The proportion of patients giving consent to participate in the study compared with the number of patients approached for the study, and the reasons for refusal to participate;2. The qualitative reasons reported by the patients for non-adherence to the program (for patients dropping out of the program);3. The qualitative barriers/facilitators reported by the patients to the program implementation;4. (a) The score of the Consumer Satisfaction Questionnaire (CSQ-8) – (Kapp et al., 2014). This scale allows the quality-of-care assessment and will evaluate the acceptance and relevance of the programs.(b) The score on the Session Evaluation Questionnaire (SEQ in order to assess the weekly satisfaction about the sessions. It takes 5 minutes and consists of 22 items. Each item represents two bipolar adjectives on which the patient ranks at the end of a therapeutic consultation. For the purposes of this study, we will consider only the first factor, the 11 items on the feeling of the session (pleasant interview, powerful, superficial, etc.) (Stiles, 1980).5. (a) The scores on the Multidimensional Fatigue Inventory (MFI-10) - (Baussard et al., 2018). This 10-items short scale is validated in cancer patients and assess physical, emotional and cognitive fatigue.(b) The scores on the VAS fatigue (Baussard et al., 2017). This VAS is adapted on the phone application (≪ Mon Essai Patient ≫) for the study needs, while respecting its original form. Patients are asked to indicate, with a cursor going from 0 to 10, their state of fatigue, whether physical (I lack energy) or psychological (I feel weariness).6. The scores on the Quality of Life (QLQ-C30 – EORTC) - (Aaronson et al., 1993). The QLQ-C30 incorporates nine multi-item scales: five functional scales (physical, role, cognitive, emotional, and social); three symptom scales (fatigue, pain, and nausea and vomiting); and a global health and quality-of-life scale. The EORTC QLQ-C30 was extensively validated in European languages, including French;

**Table 1 T1:** Description^1^ of the sessions for both programs.

	**Hypnosis**	**CBT**
Session's themes		
Each session ends with a debriefing and Questions/Answers		
Fatigue education	Program presentation Fatigue education Short hypnosis session: “Safe place” induction Questions/Answers	Program presentation Fatigue education Introduction to CBT Questions/Answers
Perceived control	Induction with sensory data collection (fatigue as a deep feeling of tiredness) Miracle question and search for exception based on Solution-focused therapy	Discussion about patient's representations of fatigue and cancer Exercise on causal attributions (internal, external and hazard) To think about action to implement to regain control over fatigue
Emotional regulation	Induction on breathing Safe place and work on emotion observations and rating Anchoring the feeling of wellbeing	To identify feelings and associated thoughts To list problematic situations To notice dysfunctional thoughts and searching for alternative thoughts
Social support	Questioning about relatives support and induction on today fatigue sensation Rossi's mirroring hands to identify people who are social resources	Presentation of social support and its dimensions To identify people resources for each type of support To learn how communicate needs and assertiveness
Coping strategies	Induction with body scan to focus on a specific site where fatigue is intense (e.g., shoulders or legs) Work on metaphors and reifying the symptom	Presentation of coping strategies To think about patient's behaviors and coping efficacy (Cunji's circle) To consider alternative behaviors
Synthesis	Feedback on the program and on the exercises that need to be repeated To see with the patient where he/she stands	Feedback on the program and on the exercises that need to be repeated To see with the patient where he/she stands

*For the content of the programs (CBT and Hypnosis), each therapist will follow a guide where each session is described (how to introduce the session, exercises during the session, at-home practices, etc.). These built guides are the property of the authors and can be provided on an argued request of interested parties (replications, systematic review)*.

*Each session from 2 to 6. Begins with a debriefing on the previous session (feedback on home exercises for CBT; feedback on experience if self-hypnosis for Hypnosis)*.

### Measures

In this feasibility study, the primary endpoint is the proportion of patients who have adhered to the proposed intervention program (both CBT and hypnosis programs include 6 sessions). A patient will be considered adherent if she/he participated in at least 4 of the 6 proposed intervention sessions. Adherence is defined in the same way in each intervention group. The choice to consider adherence to the programs at 4 out of 6 sessions is a commonly accepted practice in non-medication intervention studies (Brebach et al., 2016). Thus, patients participating in the study will have to receive at least 4 sessions (addressing key issues related to fatigue) in order to consider the program beneficial (hypnosis or CBT).

There are secondary quantitative and qualitative endpoints:

#### Semi-directed interviews

Qualitative interviews are planned to assess the relevance of the programs. The interviews will be semi-structured to obtain as much information as possible. A first general question will ask about their general opinion of the program. Then, they will be asked to talk about their reasons for agreeing to participate in the program, as well as information about the implementation. Patients will answer whether the program seemed suitable or not and finally, whether they would recommend it to others. Each question is as broad as possible, and then participants will be prompted if more detail is needed. Patients who would like to end their participation in the program prematurely will also be invited to participate in these interviews, as the reasons for non-adherence are among the evaluation criteria. It is difficult to estimate the time, some patients will speak little, others elaborate more. For open-ended questions, we estimate a minimum of 20 min and a maximum of 1 h.

#### Repeated measures

Our protocol involves an ecological momentary assessment (EMA) of fatigue, ideally at the same time of day. This daily measurement of fatigue is planned from T0 to T1, i.e., 7 weeks (49 assessments). Daily fatigue assessment takes 2 min with the VAS, one for each item (Baussard et al., 2017).

Weekly satisfaction about the sessions takes 5 min and will be assessed by The Session Evaluation Questionnaire (SEQ). Each 22 item represents two bipolar adjectives on which the patient ranks at the end of a therapeutic consultation. For the purposes of this study, we will consider only the first factor: 11 items on the feeling of the session (pleasant interview, powerful, superficial, etc.) (Stiles, 1980).

### Procedure

Three time points will be considered: T0 corresponds to the patient' inclusion in the study (patient agreement and completion of the study questionnaires), T1 corresponds to the end of the intervention after 6-weeks of intervention (semi-directive interviews on the acceptability of the program and completion of the questionnaires), and T2 corresponds to a follow-up visit 3 months after the intervention (questionnaires).

During the medical consultation with the oncologist, eligible patients will be identified. After oncologist approval, only inclusion/non-inclusion criteria (including fatigue VAS) will be retrieved by the investigator. If eligible, a patient will receive the information letter and consent, and will be asked to return it for cure of chemotherapy N°1 (T0).

The investigator will collect the sociodemographic (including the Score EPICES) and the medical variables. She/he will also present a web application (smartphone or tablet), available on AppStore or PlayStore (“*Mon Essai Patient*”) from the company Exolis. Patients who are not comfortable with these tools have the option of having a paper format. This application allows to collect every data from the questionnaires, encourages the daily or weekly assessment and limits missing data because patients will receive a notification when a questionnaire must be completed. Then a clinical research associate will give the different self-questionnaires to the patient, responding her/his questions if necessary. As shown Table 2, the patient will fill out, during ~30 min, the MFI-20, theQLQ-C30, and the VAS fatigue.

**Table 2 T2:** Measurements used in the study.

**Measures**	**Screening**	**T0**	**6 weeks interventions**	**T1**	**T2**
Inclusion/non-inclusion criteria	X				
Information letter and consent		X^a^			
Sociodemographics and medical variables		X		X^b^	
EPICES score		X^c^			
Fatigue and Quality of Life:					
6. VAS fatigue (physical/emotional)	X	X	X^c^ Daily assessment		X^c^
7. MFI-20		X^c^		X^c^	X^c^
8. QLQ-C30		X^c^		X^c^	X^c^
Feasibility					
9. SEQ			X^c^		
			Weekly assessment		
10. ISQ-8				X^c^	
11. Qualitative interviews				X^c^	

a *Information letter and consent are delivered at screening and retrieved if inclusion at T0*;

b * if progression, relapse or change of treatment*;

c * E-health application; MFI-20, Multidimensional Fatigue Inventory; QLQ-C30, Quality of Life Questionnaire – Cancer; Score EPICES, precariousness and social inequalities in health; SEQ, session evaluation questionnaire; CSQ-8, satisfaction questionnaire about interventions*.

Randomization procedure. If the patient meets all the inclusion criteria and return the consent at T0, Biometrics Unit will proceed with the randomization and return the assigned treatment arm to the investigator. This form should also be completed and submitted for patients who meet the inclusion criteria but do not agree to participate in the study. A specific section of the form will be dedicated to them in order to register these patients (this will allow to answer the first secondary objective; i.e., the acceptance of participation in the study). The randomization procedure using the random block method will allocate the Hypnosis or CBT treatments with a 1:1 ratio and will be stratified according to two factors with two modalities: the number of lines of chemotherapy (2nd or 3rd line) and the management by the support care platform in the hospital (yes, no). Regarding stratification, the number of lines of treatment may have an impact on the primary endpoint (increase in fatigue) since it implies a non-response to treatment, a progression of the disease, and possibly a deterioration in the patient's condition. Secondly, the patients received at the Center may be offered support care as part of their standard care (*e.g.*, nutritional follow-up), and this may also have an impact on the primary endpoint (*e.g.*, reduction in fatigue). Therefore, these two factors will be considered as a stratification factor.

As shown in flow-chart (Figure 2), an included patient will be assigned to one of two intervention programs. Either hypnosis with 6 standardized sessions (1/week) of ~30–45 min or CBT with 6 standardized sessions (1/week) of about 1 h. In order to respect the chemotherapy pathway of CRCm patients, one session will be done face-to-face on the day of the treatment, and the following session will be offered remotely by telephone or videoconference (at a distance) when the patient is at home during the week without chemotherapy. For the three remote sessions of the intervention, patients can choose between telephone or videoconference therapy. If patients choose video, the sessions will be conducted using a secure tele-health platform called *Starleaf* (https://starleaf.com/about-us/). This company was Founded in 2008 in Cambridge and provides secure meetings, messaging and calling to enterprises worldwide. Thus, the first session of a program will take place face to face, during treatment cure N°2 (i.e. after a respected delay after the proposal to participate in the protocol), the third and the fifth respectively during chemotherapy N°3 and N°4 in hospital. The second, fourth and sixth sessions will take place remotely. Three therapists (one for the hypnosis and two for the CBT program) will implement the interventions and all patients will receive an individual notebook with explanations of the program, fatigue education, and blank pages to take notes after each session. The mail of the clinical research assistant will also be presented here if any questions arise between two sessions.

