## Introduction

In cancer patients, fatigue appears to be one of the most frequent and persistent symptoms (NCCN National Comprehensive Cancer Network, 2017). Cancer-related fatigue (CRF) has been defined as a distressing, persistent, subjective sense of physical, emotional, and/or cognitive tiredness or exhaustion related to cancer and/or cancer treatment that is not proportional to recent activity and interferes with usual functioning (NCCN National Comprehensive Cancer Network, 2017). Patients consider it severe and intense (Stone et al., 2000). Fatigue can have important psychosocial consequences such as reduced daily activities, and decreased quality of life (Lawrence et al., 2004; Forlenza et al., 2005).

Patients with metastatic colorectal cancer (CCRm) may follow several chemotherapy cycles. They follow months or even years of treatments, leading to many side effects (Wagland et al., 2015) and involving a decrease in Quality of Life (QoL) and functional status (Mayrbaeurl et al., 2016). In patients with colorectal cancer, fatigue ranks first among chemotherapy-related adverse events, with 75% of patients presenting a grade 3-4 with physical and psychological consequences (Mitry et al., 2010; Mota et al., 2012; Vardy et al., 2014). Then, metastatic progression and the increasing number of treatments are also aggravating factors (Peria et al., 2012), with a study reporting that 16% of patients in a clinical trial have fatigue graded at ¾, which corresponds to a very intense fatigue (Miyamoto et al., 2016).

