Thus, the relative efficacy of hypnosis and CBT on CRF has been described in oncology, but very few of these interventions have been conducted specifically on CRCm patients. The difficulties in implementing such programs in the care pathway underlines the importance of conducting this type of study. To our knowledge, there is no study proposing CBT or hypnosis in patients with CRC to reduce CRF. Since the implementation of two psychosocial intervention programs in a health care center is complex, and there is a need to develop standardized interventions for a specific population (CRCm patients), it was decided to first conduct a feasibility study. van Lankveld et al. (2018) suggest that feasibility studies should assess interest and willingness of patients to receive professional psychosocial care. To go further, evidence-based practice, defined as “the conscientious, explicit and judicious use of current best evidence in making decisions about the care of individual patients” (Trinder, 2008) has become an important feature of health care systems and health care policy.

Furthermore, several studies and meta-analyses underline a better effectiveness of face-to-face sessions (Montgomery et al., 2002; Schnur et al., 2008; Askay et al., 2009), and individual sessions rather than group sessions (Cousson-Gélie et al., 2011). We therefore propose individual face-to-face sessions. Beside, the programs in this study are intended to respect the chemotherapy pathway of CRC patients (i.e., a treatment every 2 weeks). This approach seems to be essential to allow a good implementation within the hospital, and not to induce an additional fatigue in patients by imposing them an additional travel.

This will also allow us to gather precise indicators (barriers/facilitators) regarding the implementation of psychosocial interventions in cancer centers, in order to meet the expectations of an increasingly personalized medicine, insisting on the essential place of support care.

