#### Eligibility

Inclusion criteria will be as follows:

1) Age ≥ 18 years2) WHO performance status ≤ 23) Progressive colorectal adenocarcinoma after first line metastatic chemotherapy4) Able to understand and read French5) Visual Analog Scale for fatigue ≥ 4: based on our previous work on metastatic CRC patients where 48% complained of moderate fatigue throughout treatment, and since our variable of interest is fatigue, we decided to include patients already fatigued (4/10 on VAS).6) Patients starting a second or third line of metastatic chemotherapy7) Patients who signed the informed consent8) Patients subscribed to a French Social Security system

The criteria for non-inclusion will be as follows:

1) Patients who do not have a telephone or devices that allow remote monitoring of sessions at home2) Presence of brain metastases3) Chronic pain evolving for more than 3 months and on morphine4) Patients who used to and/or have a regular and habitual practice in meditation, or in relaxation techniques such as yoga, hypnosis or sophrology5) Medical (neurological, psychiatric, etc.) or psychological conditions that do not allow participation in the protocol (filling out the questionnaires and the booklet, as well as following the sessions)6) Deaf patient without hearing aids7) Patient under guardianship or legal protection

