### Statistical considerations

The primary outcome will be analyzed in each intervention group. The proportions of patients who adhered to each intervention program (Hypnosis and CBT) will be presented with their two-sided 95% confidence intervals (95% CI), as the proportion of patients giving consent to participate in the study among the eligible patients at the screening who were offered the study. All statistical analyses of the secondary criteria will be done by group. Categorical variables will be described by the number of observations (N) and the frequency (%). Missing categories will be counted. Quantitative variables will be described by the number of observations (N), mean, standard deviation, median, minimum, and maximum. In case of missing data no imputation method will be used.

For the comparison of qualitative variables, a chi-square test or a Fisher's exact test will be used if the theoretical number of observations is <5. For the comparison of quantitative variables, a Student's *t-*test or a Kruskal-Wallis test will be used. For comparisons between two time points a Wilcoxon test for paired samples will be used. The correlation between the VAS values for fatigue and the scores on the MFI-10 questionnaire will be studied using Pearson's correlation coefficient or Spearman's correlation coefficient. The evolution of VAS fatigue values over the course of treatment will be modeled using linear mixed models to account for the repeated nature of the measurements. The analysis of the QLQC-38 questionnaire will be performed according to the EORTC guidelines.

All statistical tests will be two-sided and the significance level is set at 5% (i.e., *p* < 0.05). Statistical analyses will be performed with STATA v16 software and a statistical report will be provided according to the current model.

Program satisfaction will be assessed on the basis of the CSQ-8 score, SEQ evaluation of each session and put into perspective with the individual semi-structured interviews analyzed with QDA Miner. This is a mixed methods and qualitative data analysis software developed by Provalis Research. The program was designed to assist researchers in managing, coding and analyzing qualitative data. QDA Miner was first released in 2004 and the latest version 6 was released in September, 2020.

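### Baseline fatigue and quality of life are taken a full chemotherapy cycle before session 1, so the within-arm T0-T1 change includes the first cycle of a new line as well as the program

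*Protocol article*

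**What the plan says.** Under Eligibility, entrants are "Patients starting a second or third line of metastatic chemotherapy". Under Procedure, a patient who receives the information letter and consent form "will be asked to return it for cure of chemotherapy N°1 (T0"), and the baseline questionnaires are completed at T0. The same section says that "the first session of a program will take place face to face, during treatment cure N°2", and places "the third and the fifth respectively during chemotherapy N°3 and N°4 in hospital"; sessions 2, 4 and 6 are remote, in the weeks without chemotherapy. The Introduction gives the rhythm as "a treatment every 2 weeks".

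Table 2 schedules the MFI and QLQ-C30 at T0, T1 and T2 only. Repeated measures runs the daily VAS from T0 to T1, given as 7 weeks and 49 assessments, whereas Table 2 puts it in the column for the 6 weeks of intervention.

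One secondary objective is fatigue before and after the intervention and its evolution; another is quality of life at baseline and after the intervention. Under Statistical considerations: "For comparisons between two time points a Wilcoxon test for paired samples will be used", and "The evolution of VAS fatigue values over the course of treatment will be modeled using linear mixed models". The article does not separate the time before session 1 from the time after it.

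**The concern.** A before-and-after contrast describes an intervention only if the first measurement stands close to its start. Here one infusion and a full cycle of a new regimen lie between the two. The Introduction itself says that "fatigue ranks first among chemotherapy-related adverse events", so a change in fatigue over that cycle is plausible, and it would be counted as change over the program. The trial has no untreated arm; the Discussion reserves a control arm for a later three-arm RCT.

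At stake is how the within-arm fatigue and quality-of-life results are read. A rise in the first cycle could hide a later fall during the program, and a first-cycle fall could pass for a benefit. The Discussion expects the study to show which management is most effective and for which fatigue profiles, so readers will be inclined to take these changes as program effects.

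**Working it through.** **Inputs from the protocol.** T0 at infusion 1; sessions 1, 3 and 5 at infusions 2, 3 and 4; sessions 2, 4 and 6 in the weeks between (all Procedure). Cycle length 14 days (Introduction). Daily VAS for 49 days from T0 to T1 (Repeated measures).

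**Step 1: the timeline.** Infusion k falls on day 14 × (k − 1), with T0 as day 0.

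| Event | Day from T0 |
|---|---|
| Infusion 1, T0 | 0 |
| Infusion 2, session 1 | 14 |
| Session 2 | 21 |
| Infusion 3, session 3 | 28 |
| Session 4 | 35 |
| Infusion 4, session 5 | 42 |
| Session 6 | 49 |

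T0 to session 6 is 49 days, or 49/7 = 7 weeks. This reproduces the protocol's own 7 weeks and 49 assessments, so a 14-day lead-in is consistent with its stated window.

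**Step 2: share of readings before any session.** 14/49 = 28.6%, leaving 35 from session 1 on.

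**Step 3: effect on the T0-T1 change.** Assume that fatigue rises by A points over the lead-in and then stays flat, with no program effect. A is an assumption; the protocol gives no figure for a first-cycle change. The T0-T1 change is then A − 0 = A. If instead fatigue rises by 1 point in the lead-in and truly falls by 1 point during the program, it is 1 − 1 = 0 and the fall is invisible.

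**Step 4: effect on a single linear trend.** This is one possible form of the mixed model. For noise-free readings on days d = 0 to 48 (mean 24), the least-squares slope is Σ(d − 24)y / Σ(d − 24)², with denominator 9,800.

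- Ramp reaching A on day 14: numerator 147.5A, slope 0.01505A per day. Over 48 days this is 0.72A; over 49 days, 0.74A.
- Ramp reaching A on day 13: numerator 140A, slope 0.01429A per day. Over 48 days this is 0.69A; over 49 days, 0.70A.
- Rise of 1 to day 14, then a fall of 1 by day 48: the fitted change over 48 days is −0.39 instead of −1.
- Lead-in of only 7 days, then flat: 0.43A over 48 days.

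For the nominal schedule the single trend therefore carries about 0.7A. For A = 1 to 2 points, taken only as an illustration, that is about 0.7 to 1.4 points, against 1 to 2 points in the T0-T1 change.

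**Step 5: would the mean of the lead-in readings serve as the baseline?** Under the same ramp, the mean over days 0 to 13 is 6.5/14 = 0.46A (top on day 14) or 6.5/13 = 0.50A (top on day 13). The mean of the last 14 days is A. The contrast still shows 0.50A to 0.54A with no program effect, so averaging the lead-in only halves the artefact. The level at session 1 removes it in this scenario.

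**The case against.** The strongest reply is that much of this is detail for the SAP. That stands for the model. The article fixes no time origin, functional form or covariates for the VAS, and a piecewise model with a change point is also a linear mixed model. A reader might infer that one straight line over 49 days is planned; the text does not say so, and the 0.7A figure shows only what that form would do. The reply does not reach the schedule, which the article fixes: no analysis can create an MFI or QLQ-C30 value at session 1.

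Three other readings go too far.

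- *T1 is mid-cycle.* Session 6 nominally falls 7 days after infusion 4, so one might infer that T1 compares a mid-cycle day with an infusion day. But Procedure says only that T1 follows six weeks of intervention, and the Figure 2 legend lets sessions shift by 1 or 2 weeks. The cycle day of T1 is not fixed.
- *The later RCT would inherit a wrong effect and SD.* The article says that results will generate hypotheses and encourage an RCT. It does not say that an effect size or SD will be carried forward.
- *The arm comparison is biased.* Randomization takes place at T0 and both arms share the lead-in, so it is not; at most the lead-in adds noise.

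It is also fair that the size is assumed. The fatigue profiles in the Discussion put 11.83% of patients in the increasing class. These describe whole treatment courses, so they neither support nor refute a first-cycle rise. Finally, chemotherapy continues during the program, so no choice of time origin lets within-arm change isolate the program.

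**Conclusion.** The point holds for a secondary, within-arm objective. On the protocol's own schedule, the only MFI and QLQ-C30 values before the program are taken nominally 14 days and one full cycle before session 1, at the start of a new line. 14 of the 49 daily VAS readings (29%) also precede session 1. Any lead-in change of A points passes in full into the T0-T1 change, and about 0.7A passes into a single linear trend if that form is used.

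The timing rests on the nominal 14-day cycle and can vary between patients because sessions may shift. The value and sign of A are unknown. The primary endpoint (at least 4 of 6 sessions attended) is untouched. The point is worth acting on because the readings needed to separate the lead-in from the program are already planned.

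**What to change.** 1. **VAS model.** Set time zero at each patient's actual session 1, with a change point there that separates lead-in from program phase, and add day since last infusion as a covariate.
2. **VAS change.** Base the program-phase change on the model's level at session 1 or on the readings just before it, not on T0 and not on the 14-day lead-in mean.
3. **Data collection.** Reconcile Table 2 (daily VAS under the 6-week intervention column) with Repeated measures (T0 to T1, 7 weeks), so that the lead-in readings are collected.
4. **MFI and QLQ-C30.** State that T0-T1 change includes the first cycle of the new line and is not a program effect. Fix the cycle day of T1, matching T0 where a scheduled visit allows.

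The cost is slightly more analysis work and some wording. If T1 is matched to an infusion day, the questionnaires may come up to a week later; on the nominal schedule that is day 56, an infusion 5 that the article does not mention, hence the condition on a scheduled visit. No session or treatment has to move. Even then, chemotherapy during the program still confounds within-arm change, and the report should say so.
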